## Methods/design

Participants will be inactive people aged 18 to 74 years who are eligible to be referred by their GPs for an exercise intervention. Participants will be people with hypertension or high-normal blood pressure and assessed as being inactive or moderately inactive using the General Practice Physical Activity Questionnaire (GPPAQ) screening tool. The inclusion and exclusion criteria are detailed below.

The study will be conducted in the Guildford and Waverley CCG area (Surrey, UK) and patients will be recruited via GP surgeries serving catchment areas within reasonable reach of Surrey Sports Park and the five DC leisure centres in Waverley, Surrey, UK. We have designed the study with the intention to allow recruitment for all patients eligible for an exercise referral within the 9 months of the proposed trial data collection phase.

The trial design is shown in Figure 1. The key features are that, after a patient has been assessed as likely to benefit from an exercise intervention, their referral is to the project research assistant who will allocate the patient to one of four conditions on the basis of previous independent randomisation. These are: 1) GP gym-based referral (GPGR, the treatment as usual control); 2) GP gym-based referral plus web tool (GPGR + WEB); 3) sport referral at Surrey Sports Park (SPR); and 4) sport referral at Surrey Sports Park plus web tool (SPR + WEB). After obtaining informed consent patients attend a 12-week exercise programme (sport or gym) and their activity levels and sporting participation are monitored again at 6 months and 12 months after starting the exercise programme. Pending ethical approval the intention is to commence recruitment in the early autumn of 2013 for a period of 9 months.

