**Trial design diagram.**

The inclusion criteria are as follows:The patient is aged 18 to 74 years at randomisation.The patient has been diagnosed as having hypertension or high-normal blood pressure as recorded on their GP records and is regarded by their GP as someone who would benefit from attending an exercise programme. High-normal blood pressure is defined as systolic blood pressure 130 to 139 mmHg or diastolic blood pressure 85 to 89 mmHg based on clinical records.The patient is screened as being ‘inactive’ or ‘moderately inactive’ on the GPPAQ.The patient has access to the internet and an email account.The patient is able to understand the Informed Consent Form, and understand study procedures.The patient has signed the Informed Consent Form.

The exclusion criteria are as follows:The patient is pregnant.Inability to freely consent to take part in the studyInability to understand the study materials.The patient is unable to access the internet/emailCurrent participation in another clinical trial relating to physical activity or exerciseAny condition that, in the GPs opinion, compromises the subject’s ability to meet protocol requirements or to complete the study.The patient is referred out of the trial by the exercise professional on the grounds that the programme is, in their judgement, likely to cause harm.

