### Sample size and power calculations and randomisation

Davies and colleagues report a meta-analysis of internet-based exercise intervention studies which suggests an average effect size of d = 0.14
[16]. A Cochrane review of general interventions to promote activity among inactive adults reports an average SMD = 0.28, but notes considerable heterogeneity in effects sizes
[4]. In the case of internet interventions aimed at reducing blood pressure, effects sizes of the order of SMD = 0.27 and 0.17 for systolic and diastolic blood pressure, respectively (equating to drops of 3.8 and 2.1 mmHg, respectively), have been identified in a recent meta-analysis
[35]. Based on these analyses, an effect size of 0.125 can be assumed for comparing means of MET-minutes per week and mmHg between the intervention and control arms (equinumerous) for a two-arm study. With this effect size, if each arm consists of 500 subjects, a power of 80% is obtained for a two-sided statistical contrast to show statistical significance, at the 5% level, of the difference of the means of the two arms with respect to these outcome variables. It is therefore decided that there will be 500 subjects in each of the four arms of the present study.

Block randomisation is to be conducted by the University of Surrey’s Clinical Research Centre. Participants cannot be blinded to the nature of the intervention they are receiving and for reasons of monitoring and contacting participants the research assistant also cannot be blinded. The primary analyst will be blinded to participant allocation.

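### The order of consent and allocation is unreconciled, and an untimed referral-out exclusion lets randomised patients leave the sport v gym comparison

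*Protocol article*

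**What the plan says.** The narrative in Methods/design runs in this order: GP assessment; then "their referral is to the project research assistant who will allocate the patient to one of four conditions", which continues by tying the assignment to an independent randomisation made beforehand; then the list of four arms; then "After obtaining informed consent patients attend a 12-week exercise programme (sport or gym"). The section on sample size and randomisation adds that "Block randomisation is to be conducted by the University of" Surrey's Clinical Research Centre, and that "for reasons of monitoring and contacting participants the research assistant also cannot be blinded".

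The inclusion criteria refer the age limit to randomisation and end with "The patient has signed the Informed Consent Form". The last exclusion criterion reads "The patient is referred out of the trial by the exercise professional on the grounds that the programme is", in that professional's judgement, likely to cause harm. It gives no time and names no programme.

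Measures has the exercise professional taking health measurements at the start, middle and end of the 12-week programme. Intervention effectiveness fixes the analyses as per protocol and states no intention-to-treat analysis.

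**The concern.** Two routes could select patients after randomisation.

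- **Refusal.** If the narrative order is followed, a patient may know the arm before deciding on consent. Someone who then declines fails an inclusion criterion after having been allocated.
- **Removal.** A patient can be taken out of the trial, not only out of the programme, on a judgement about a programme that differs between the sport and gym arms. The professional who makes that judgement is described as meeting patients at the programme.

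Willingness and physical suitability plausibly relate to activity at 12 months. If losses differ between sport and gym, the remaining groups are no longer those that randomisation created. The per-protocol rule means that no stated analysis puts these patients back.

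**Working it through.** **1. Order of consent and allocation.** There are two readings, and both cannot be operated.

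- Narrative in Methods/design: allocation, then consent, then the programme. Consent may follow knowledge of the arm.
- Inclusion criteria: signed consent is a condition of entry and age is judged at randomisation. This points to consent first, in which case the narrative misplaces it.

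The text does not settle which is meant.

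**2. Timing of the referral-out exclusion.** It stands in an eligibility list, which suggests that it acts before entry. But it depends on the programme, the programme depends on the arm, and Measures places the exercise professional at the programme from its first session. As written, it can act after allocation.

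Gym v gym plus web, and sport v sport plus web, share the same exercise programme. A programme-based removal rule should therefore bear much less on those contrasts than on sport v gym. Refusal after learning the arm, if it can occur, is not limited in this way.

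**3. Analysis set.** Per protocol is the only stated basis, so a patient lost by either route has no stated place in the comparison.

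**4. Size, by illustration.** From the sample size section: planning effect 0.125 SD, 500 per arm, two-sided 5%. The stated 80% power does not reproduce from these: 0.125/√(2/500) − 1.96 = 0.016, which gives 50.7%. That is a separate matter. Only the 0.125 SD is used here, as a yardstick.

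Assumed, because the documents give no rates: a fraction f is lost from one arm only, and those lost average g SD below the whole arm's mean. The remaining mean then shifts by b = f·g/(1 − f). The type I error uses SE = √(1/500 + 1/(500(1 − f))).

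| f | b for g = 0.25 to 1.0 | share of 0.125 SD | type I error |
|---|---|---|---|
| 2% | 0.005 to 0.020 | 4% to 16% | 5.1% to 6.2% |
| 5% | 0.013 to 0.053 | 11% to 42% | 5.5% to 13% |
| 10% | 0.028 to 0.111 | 22% to 89% | 7% to 40% |

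If both arms lose patients, the bias is the difference of the two shifts. With g = 0.5:

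- 10% v 3%: 0.5×0.10/0.90 − 0.5×0.03/0.97 = 0.056 − 0.015 = 0.040 SD.
- 25% v 10%: 0.5×0.25/0.75 − 0.5×0.10/0.90 = 0.167 − 0.056 = 0.111 SD.

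If the 0.5 SD gap is measured from those who remain, the bias is g times the difference in fractions: 0.5×0.07 = 0.035 SD and 0.5×0.15 = 0.075 SD. The shares of 0.125 SD fall from 32% and 89% to 28% and 60%. Equal losses of similar patients give zero. None of these figures allows for the planned adjustment for baseline activity.

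**The case against.** The article describes only key features and refers to a design figure that is not shown. Four stronger readings are tempting, and the documents do not support them.

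- **Allocation is known to precede consent.** This rests on sentence order. The sentence on consent says that it comes before the programme, not that it comes after allocation, and the inclusion criterion points the other way. What stands is a conflict between two parts of the text.
- **The research assistant controls or can foresee the assignment.** The assistant works from an independent randomisation conducted by the Clinical Research Centre, and the stated reason for being unblinded is monitoring and contacting participants. Nothing shows that the next assignment is visible. An article may leave concealment details to the full protocol, so no finding is made on that.
- **Removal is arm-specific.** The criterion names no arm. The Background says that the professional will take other medical conditions into account so that sessions are safe, which makes differential removal less certain. Dependence on the allocated programme is the natural reading, since the programme differs by arm, but it is an inference.
- **The bias approaches the planning effect.** The upper figures come from chosen inputs. They depend on how the gap is defined, and adjustment for baseline activity could remove part of any bias.

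The per-protocol rule is also a wider issue in its own right. Here it matters only because nothing else stated would restore patients lost by these two routes.

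**Conclusion.** The point holds in a limited form. The Methods/design narrative and the inclusion criteria disagree on where consent falls. The referral-out exclusion has no stated time and is given to someone whom the document places at the programme. Followed as written, and with per-protocol analysis alone, the plan allows randomised patients to leave the sport v gym comparison for reasons related to the allocated programme. The web-tool contrasts within one programme are less exposed to removal.

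The size cannot be determined from the document. Under the assumed one-arm losses it runs from 0.005 SD (4% of the 0.125 SD planning effect) to 0.111 SD (89%), and it is nil if losses are alike. The range shows that modest differential loss could matter against so small an effect. It does not show that such loss occurs.

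**What to change.** - Reconcile the narrative with the inclusion criteria by stating that eligibility, consent and baseline measures are complete before the allocation is revealed.
- State that the referral-out exclusion applies only before allocation. It then cannot refer to the allocated programme, so suitability has to be considered for both programme types.
- Keep anyone later stopped from a programme in the 6- and 12-month follow-up, and analyse them in the allocated arm.
- For patients already allocated, report refusals and removals by arm.

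The exercise professional's freedom to stop a programme is unchanged. Only the patient's membership of the trial and of the analysis is affected.

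The cost is a small amendment to the enrolment sequence and the effort of following people who have left the programme. The first health measurements, now placed at the start of the programme, would also have to be taken before the arm is disclosed. Recruitment began in October 2013 and data collection is continuing, so the new sequence can apply only to patients not yet allocated.

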**Figure 1 Fig1:**
[figure not shown]
**Trial design diagram.**

The inclusion criteria are as follows:The patient is aged 18 to 74 years at randomisation.The patient has been diagnosed as having hypertension or high-normal blood pressure as recorded on their GP records and is regarded by their GP as someone who would benefit from attending an exercise programme. High-normal blood pressure is defined as systolic blood pressure 130 to 139 mmHg or diastolic blood pressure 85 to 89 mmHg based on clinical records.The patient is screened as being ‘inactive’ or ‘moderately inactive’ on the GPPAQ.The patient has access to the internet and an email account.The patient is able to understand the Informed Consent Form, and understand study procedures.The patient has signed the Informed Consent Form.

The exclusion criteria are as follows:The patient is pregnant.Inability to freely consent to take part in the studyInability to understand the study materials.The patient is unable to access the internet/emailCurrent participation in another clinical trial relating to physical activity or exerciseAny condition that, in the GPs opinion, compromises the subject’s ability to meet protocol requirements or to complete the study.The patient is referred out of the trial by the exercise professional on the grounds that the programme is, in their judgement, likely to cause harm.

### Measures

PA will be assessed via an online questionnaire using the short-form version of the International Physical Activity Questionnaire
[29], which is a well validated measure of physical activity in a number of domains and permits the calculation of MET per minute values for activities in each domain, including leisure and sporting activity
[30]. As recent research has shown that the International Physical Activity Questionnaire can overestimate activity in sedentary individuals we will use a second validated self-report measure, the Self-Report Walking and Exercise Tables
[31] that also permits the estimation of MET minutes. We will include additional items to tap the types of sporting activity people do.

Participants will complete the GPPAQ screening tool at the beginning and end of the study for inclusion on their patient records.

Health indicators will include measures of height and weight (body mass index (BMI)), waist and hip circumference, and blood pressure. These measures will be assessed by the exercise professional at the beginning, middle and end of the 12-week exercise programme. They will be collected again at the end of the 12-month period on visiting their GP surgery. Patients will be asked to consent to the collection of their most recent blood sugar, cholesterol/high-density lipoprotein ratio and indications of whether they are receiving treatment for high blood pressure. We will ask for access to medical records to assess whether they have chronic kidney disease, diabetes, rheumatoid arthritis or atrial fibrillation. These indicators are required for the QRisk2 calculations. To assess safety we will also monitor well-being during the period of the exercise programmes. Blood pressure measurements will be taken by the research team and/or by specially trained exercise professionals using Omron M6W blood pressure monitors (Omron Health Care Co. Ltd, [name]).

General health will be assessed with the RAND SF36
[32] along with short measures of drinking (the AUDIT
[33]) and smoking behaviour (The Fagerstrom Test
[34]). These will be assessed at baseline and at 12 month follow-up.

Intervention exposure will be assessed by attendance at the exercise programme sessions. Web-tool usage will be assessed by number and duration of logins over the study period.

Patient evaluation of, and responses to, the interventions will be assessed by a short online questionnaire. This will assess what they felt about the interventions on rating scales, the degree to which assumed mediator variables were influenced by the interventions (for example, perceptions of control and autonomy) and it will collect free-form comments about the interventions. Views about the trustworthiness of web sources of exercise advice will be assessed.

Patient orientation towards activity will be assessed by a short series of questions to assess control beliefs and autonomy over choosing to do physical activity, intentions and motivations.

Demographic and background information will include gender, age, ethnic origin, occupation, marital status and postcode (for assessment of socioeconomic deprivation). They will be asked if there is a family history of premature coronary heart disease. Participants will be asked about their use of GP websites and other online health and well-being sites.

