**Methods/design:**

Four-arm randomised controlled trial. The study tests two types of intervention that are intended to increase physical activity among currently inactive 18- to 74-year-old people with hypertension or high-normal blood pressure. This study will assess the effectiveness of a 12-week sports-oriented exercise programme, the efficacy of a web-delivered self-help tool to promote and support sports participation and healthy behaviour change and the effect of these interventions in combination. The control arm will be a standard care general practitioner referral for gym-based exercise. Participants will be allocated using block randomisation. The first author and primary analyst is blinded to participant allocation. The primary outcome measures will be time spent in physical activity assessed in metabolic equivalent minutes per week using the International Physical Activity Questionnaire 1 year after commencement of the intervention. Secondary outcomes include increased involvement in sporting activity and biomedical health outcomes including change in body mass index, and waist and hip measurement and reductions in blood pressure.

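### The 6- and 12-month assessments are counted from programme start, and waist, hip and blood pressure baselines follow allocation, so randomised non-starters have no outcome date and may lack those baselines

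*Protocol article*

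**What the plan says.** In the protocol article, Methods/design, the referral goes to the research assistant, who will "allocate the patient to one of four conditions on the basis of previous independent randomisation". Once consent is given, patients enter the sport or gym course of 12 weeks. On follow-up, the section says: "their activity levels and sporting participation are monitored again at 6 months and 12 months after starting the exercise programme". The Abstract places the primary outcome "using the International Physical Activity Questionnaire 1 year after commencement of the intervention".

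For BMI, waist, hip and blood pressure, Measures states: "These measures will be assessed by the exercise professional at the beginning, middle and end of the 12-week exercise programme". It then adds: "They will be collected again at the end of the 12-month period on visiting their GP surgery". The same section lets the research team, as well as trained exercise professionals, measure blood pressure, and has activity collected by online questionnaire.

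Three other statements bear on the point. Sample description lists weight, height and BMI among the characteristics recorded at screening. Intervention effectiveness uses the baseline activity score as the covariate for the primary outcome. That section also makes the analyses per-protocol.

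**The concern.** Starting the programme happens after randomisation and depends on what the patient does. Using it as time zero has three consequences.

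- A randomised patient who never starts has no date on which the primary outcome falls due.
- If the wait for a place differs between gym and sport, the arms are assessed at different times since randomisation, and possibly in different seasons.
- In the web arms, commencement of the intervention could be read as first use of the web tool, so the Abstract and Methods/design need not give the same date.

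The health indicators have a related problem. If waist, hip and blood pressure are first measured at the beginning of the assigned programme, the baseline is taken after allocation by staff who would know whether the patient is in sport or gym, and it requires the patient to turn up. An analysis of all randomised patients could then not be rebuilt later for change in these measures, because the data were never scheduled.

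**Working it through.** **1. Order of events.** Methods/design gives referral, then allocation, then the 12-week programme, with follow-up at 6 and 12 months from its start. The Abstract gives one year from commencement of the intervention. Neither clock starts at randomisation, and neither place says what applies to someone who does not start.

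**2. Which baselines depend on starting.**

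| Measure | Earliest measurement stated | Depends on starting? |
|---|---|---|
| Activity (primary outcome) | Baseline score, online (Measures; Intervention effectiveness) | No |
| SF36, AUDIT, Fagerstrom | Baseline (Measures) | No |
| Weight, height, BMI | Screening (Sample description); also beginning of programme (Measures) | No, but the two sections differ on timing |
| Waist, hip | Beginning of programme (Measures) | Yes |
| Blood pressure | Beginning of programme (Measures); the research team may measure, but no earlier occasion is scheduled | Yes, as scheduled |

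The blood pressure used for the high-normal eligibility criterion comes from clinical records, not from the monitor that Measures specifies, so it is not a trial baseline.

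**3. What needs the missing baselines.** Research questions and hypotheses sets blood pressure success as a mean fall of 2.5 mmHg, and as more than 20% of an arm falling by over 10 mmHg. Intervention effectiveness compares that proportion by chi-square. Both are changes from baseline, so a non-starter without a trial baseline cannot be classified. A t-test on 12-month values alone would not need it.

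**4. The plan's power figure.** Inputs from the sample size section: d = 0.125, n = 500 per arm, two-sided 5%. Power = Φ(d·√(n/2) − 1.96) = Φ(0.125 × 15.81 − 1.96) = Φ(0.016) = 50.7%. The stated 80% is not reproduced; it would need 1,005 per arm. A comparison of 1,000 with 1,000 (pooled factorial margins) gives 79.8%, but the section describes a two-arm contrast with 500 per arm. This mismatch is a separate matter and is used here only as the starting point.

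**5. Illustration of lost numbers.** Assume a fraction f of each arm never starts and is not measured, so n = 500(1 − f):

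| f (assumed) | n per arm | Power at d = 0.125 |
|---|---|---|
| 0% | 500 | 50.7% |
| 5% | 475 | 48.7% |
| 10% | 450 | 46.6% |
| 20% | 400 | 42.4% |
| 30% | 350 | 38.0% |

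**6. Illustration of bias.** Suppose non-start differs between two arms by 10 percentage points, non-starters lie 0.5 SD below starters in both arms, and only starters are analysed. The comparison shifts by 0.10 × 0.5 = 0.05 SD, and 0.05/0.125 = 40% of the planned effect. All of these inputs are assumed.

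**The case against.** The strongest case on the other side has five parts.

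- **The clock suits the question.** The trial asks whether activity persists after a 12-week programme, and counting from its start keeps time since the programme constant. This stands as a real trade-off, but it gives non-starters no date and does not protect the arms from differing delays.
- **A journal article need not carry every date rule.** A substitute date for non-starters may exist in the full protocol, and the trial diagram is not shown. This partly stands. The finding does not rest on silence, however: the article itself states the anchor and the occasion of the first health measurement.
- **Non-starters can still be measured.** Activity is collected online, and the 12-month health measures are taken at the GP surgery; nothing says that either is withheld. This stands, and it means that the losses in the table need not occur for activity.
- **The per-protocol rule could remove non-starters whatever the clock.** This stands, so changing the clock is not enough.
- **Differential delay is not shown.** Sport sessions are spread over the week and can be joined without booking. On the other side, the Discussion names providing suitable sport sessions as a challenge of uncertain feasibility. Delay may differ by arm; the article does not establish that it does.

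A reader might also infer that non-starters have no baseline at all, or that differing uptake is the trial's own hypothesis. The article supports neither. Weight, height, BMI and online activity have baselines that do not depend on starting, and the stated hypothesis concerns persistence. Nor does Measures say that the first measurement takes place at an exercise session; it says only that it is at the beginning of the programme.

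**Conclusion.** The point holds in limited form. Follow-up for activity, including the primary outcome, is tied to a post-randomisation event that non-starters never reach and whose timing may differ by arm. The Abstract and Methods/design describe that event differently. Waist, hip and blood pressure are first scheduled after allocation, in the assigned programme, so non-starters may lack these baselines, and the blood pressure change criteria depend on one of them. Weight, height, BMI and baseline activity are not affected, although Measures and Sample description should be reconciled on when weight is taken.

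The size cannot be derived, because the article gives no non-start rate. The power and bias figures are illustrations under assumed rates, and the 50.7% they start from reflects the separate sample size discrepancy, not the timing rule. The change is worth making because it is inexpensive and reduces selection and measurement bias arising after randomisation.

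**What to change.** - Count the 6- and 12-month assessments from the randomisation date for every randomised patient, and use the same wording in the Abstract and Methods/design.
- Send the online activity questionnaire to everyone at those dates, whether or not they start.
- Take baseline activity, waist, hip and blood pressure after consent and before allocation is released; the research team may already measure blood pressure. State in one place when weight is measured.
- Replace the per-protocol analysis, or accompany it, with an analysis of all randomised patients. Without this, the data gained on non-starters would not enter the comparison.

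The cost is an already planned measurement moved earlier and a reworded date rule. The downside is that patients who start late will be assessed slightly less than 12 months after programme start. Recording the start date would let a supplementary analysis take that into account.
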